#### Economic evaluation

Cost-effectiveness analysis will be undertaken to evaluate the full cost of this intervention and whether it yields value for money. National unit costs for specific items of service will be used to estimate the costs of services used. Primary analysis will estimate quality-adjusted life years (QALYs) from the EQ-5D-5 L using the value set recommended by the National Institute for Health and Care Excellence (NICE) at the time of the analysis [45]. Current value sets include the EQ-5D-5 L specific utility weights [46] and the crosswalk algorithm to map the EQ-5D-5 L survey to the EQ-5D-3 L value set [47]. QALYs gained between baseline and follow-up interviews (13 and 26 weeks) will be estimated as the number of weeks multiplied by the utility of observed survival. Covariates that affect costs or outcomes from relevant published economic evaluations will be identified [48]. Adjusted costs and QALYs will be bootstrapped to estimate pairs of net costs and QALYs. These will then be used to estimate the probability that the intervention may be cost-effective. Net benefit will be estimated by valuing net QALYs to reflect decision makers’ willingness to pay (WTP) for one QALY. Recent decisions by the NICE suggest that WTP is at most £20 k [49, 50]. Cost-effectiveness planes and cost-effectiveness acceptability curves (CEACs) will be plotted to summarize uncertainty associated with incremental cost-effectiveness ratios by the probability that the intervention in question is cost-effective [51].

This economic model will be varied to explore uncertainty arising from study design decisions by using higher and lower sets of unit costs; an earlier estimate of utility from the EQ-5D-5 L [47]; BADLS, the primary outcome measure, or the DEM-QoL to measure health benefit; different approaches to missing data (for example by analysing only complete cases) and predicting costs and QALYs over longer time horizons (for example 5 and 10 years).

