### Intervention

The manualised intervention adds specialist equipment and advice by trained DSPs to TAU. It provides up to 6 hours contact with a DSP for the person with dementia and the identified carer (jointly referred to as participants). DSPs design and deliver a package of memory aids up to a maximum of £150 for the person with dementia to use at home. The package for each depends on their needs, preferences and existing use of memory aids. DSPs also advise on improving everyday memory skills and on using these aids to reduce memory lapses. The follow-up sessions address queries from participants and record whether aids are appropriate to the identified goals and needs and used accordingly. Further details about the implementation of the intervention are provided in Fig. 2.

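### The stated QALY formula, weeks times utility, gives quality-adjusted weeks for an outcome named and priced in years, and does not fix which utility applies to each interval

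*Protocol article*

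**What the plan says.** All of the relevant text is in the protocol article, mainly under Economic evaluation.

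- **Outcome and unit.** "Primary analysis will estimate quality-adjusted life years (QALYs) from the EQ-5D-5 L".
- **Formula.** The quantity is described as "QALYs gained between baseline and follow-up interviews (13 and 26 weeks") and "will be estimated as the number of weeks multiplied by the utility of observed survival". No division by 52 appears. The sentence does not say whether the utility at the start of an interval, the utility at its end, or their mean is used.
- **Valuation.** "Net benefit will be estimated by valuing net QALYs to reflect decision makers’ willingness to pay (WTP) for one QALY". The price is then given: "Recent decisions by the NICE suggest that WTP is at most £20 k".
- **Adjustment.** "Adjusted costs and QALYs will be bootstrapped to estimate pairs of net costs and QALYs". The covariates are to be drawn from published economic evaluations; baseline utility is not named.
- **Timing.** Under Data collection, interviews take place at baseline, 13 weeks and 26 weeks, so there are two 13-week intervals.
- **Scale of cost.** Under Intervention, "DSPs design and deliver a package of memory aids up to a maximum of £150", with up to 6 hours of practitioner contact.

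**The concern.** The section gives an operational formula whose unit does not match the outcome it defines. Weeks times utility is a number of quality-adjusted weeks. The result is then to be multiplied by a price for one quality-adjusted year. Anyone who programmes the sentence as printed gets a QALY difference, a net benefit and an acceptability curve that are wrong in scale by a factor of 52.

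Correcting the unit leaves a second, smaller gap. There are three utility measurements and two intervals, and several rules for combining them fit the sentence. Each gives a plausible QALY total, so a reader of the results could not tell which had been used. The listed sensitivity analyses vary unit costs, the utility source, the measure of benefit, the handling of missing data and the time horizon. None varies the QALY rule itself.

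**Working it through.** The article states no QALY or net-benefit figure, so there is none to reproduce. It also gives no utilities, so those below are assumptions chosen only to show scale. The inputs taken from the article are the assessment times (0, 13 and 26 weeks), the formula, and the £20,000 ceiling per QALY.

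**Step 1: unit, one person.** As written: weeks × utility. In years: (weeks/52) × utility.

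| Assumed constant utility | As written, 26 × u | In years, (26/52) × u |
|---|---|---|
| 1.00 | 26 | 0.50 |
| 0.90 | 23.4 | 0.45 |
| 0.75 | 19.5 | 0.375 |
| 0.60 | 15.6 | 0.30 |

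The ratio is 52 in every row. No participant can accrue more than 0.5 QALY in 26 weeks.

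**Step 2: unit, between-group difference.** Assume equal baselines and a utility difference d of 0.02 at both 13 and 26 weeks, using the mean of start and end values in each interval.

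- Weeks: 13 × (0 + 0.02)/2 + 13 × (0.02 + 0.02)/2 = 0.13 + 0.26 = 0.39.
- Years: 0.39/52 = 0.0075 QALY.
- Valued correctly: 0.0075 × £20,000 = £150.
- Valued without conversion: 0.39 × £20,000 = £7,800.
- With d = −0.02 the same steps give −0.0075 QALY, −£150 and −£7,800.

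The factor enlarges a benefit and a harm alike.

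**Step 3: which utility applies.** After division by 52, let d13 and d26 be the differences at 13 and 26 weeks, with no difference at baseline. Four readings are compared:

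- mean of start and end (trapezium): [13 × d13/2 + 13 × (d13 + d26)/2]/52
- end-of-interval value: (13 × d13 + 13 × d26)/52
- start-of-interval value: (13 × 0 + 13 × d13)/52
- final value throughout: 26 × d26/52

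| Assumed path (d13, d26) | Trapezium | End value | Start value | Final value |
|---|---|---|---|---|
| 0.02, 0.02 | 0.0075 | 0.0100 | 0.0050 | 0.0100 |
| 0.06, 0 | 0.0150 | 0.0150 | 0.0150 | 0 |
| 0, 0.02 | 0.0025 | 0.0050 | 0 | 0.0100 |

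The other rules fall above, on or below the trapezium depending on the path. Nothing in the article fixes the path.

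**Step 4: baseline utility.** In the trapezium, baseline utility carries weight (13/2)/52 = 0.125. An assumed chance baseline imbalance of 0.02 therefore adds 0.125 × 0.02 = 0.0025 QALY directly, or £50 at £20,000, before any persistence to later visits. This is why baseline utility belongs among the covariates once the rule is written out.

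**The case against.** The strongest reply is that this is loose wording in a condensed article. The outcome is named in years and the price is per QALY, so the intended unit is plain. A half-year trial reporting more than 0.5 QALY per person would be noticed at once. The interpolation rule and covariate list are details that an article commonly leaves to a fuller plan, which is not shown here.

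Much of this stands. It lowers the severity, and it means that silence on interpolation or on baseline utility would not be an error by itself. It does not remove the unit point: the article does not leave the formula out, it states one, and the one stated is wrong for the unit being priced.

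A reader might be tempted to go further in four ways that the document does not support.

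- *That QALY gain and net benefit would be overstated.* The factor of 52 acts on either sign, and step 3 shows no fixed direction for the interval rule.
- *That the plan rejects the area under the curve.* The sentence refers to baseline and to both follow-ups. It neither specifies nor excludes that method.
- *That valued benefit would be wrong by £75 to £150 per pair, enough to matter beside the £150 cap on aids.* Such figures come from assumed gains. For example, with 0.03 at both follow-ups the end-value rule gives 0.0150 QALY (£300) and the trapezium 0.01125 (£225). The end-value rule is stated nowhere in the article.
- *That the delay of about 2 weeks to the first practitioner visit (Random allocation) favours the trapezium.* It need not. If a gain of 0.03 began in full at week 2, the true area would be 0.03 × 24/52 = 0.0138 QALY. The end-value rule (0.0150) would be about 8% high and the trapezium (0.01125) about 19% low.

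Nor can it be said that QALYs go unadjusted: adjustment is planned, with the covariates still to be identified.

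**Conclusion.** The point holds as a stated error of unit: the formula gives quality-adjusted weeks, 52 times the QALY that the same section defines and prices. Taken literally it would misstate the size of any QALY difference, and of net benefit, in either direction. The factor of 52 is exact on a 52-week year and needs no assumption about utilities; the pound figures rest on the assumed differences.

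The sentence also leaves open which utility applies to each interval. That is worth settling while the sentence is being corrected, but the size and sign of its effect depend on an unknown utility path, and no bias is claimed.

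Severity is minor to moderate. The error would probably be caught before results were reported, and the primary clinical outcome (BADLS) and the sample size are untouched.

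**What to change.** Replace the sentence under Economic evaluation with a rule of this kind: for each participant, QALYs are the sum over the two intervals (baseline to 13 weeks, 13 to 26 weeks) of (weeks/52) × the mean of the EQ-5D-5L utilities at the start and end of the interval, with utility set to 0 from death. In symbols, with all three interviews on schedule: QALY = (13/52) × (u0 + u13)/2 + (13/52) × (u13 + u26)/2.

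Add that baseline EQ-5D-5L utility is among the covariates for the adjusted QALY difference. If a fuller economic plan already contains these rules, it is enough to align the article's sentence with it.

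The cost is a sentence or two of text. Utilities at all three times are already being collected, so no new data are needed.

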#### Process data analysis

This analysis will use the framework in Fig. 2. Again, continuous variables will be reported by means and standard deviations and categorical variables by counts. Both standardised and study-specific measures will need analysis of covariance to identify predictive factors.

#### Qualitative data analysis

Thematic and narrative analysis of interview transcripts will be undertaken to elicit the experiences of people with dementia and their carers. At least two researchers will analyse each transcript. Once all issues have been identified, an iterative process will be used to identify the major themes and processes through conceptual abstraction. Achievement of data saturation will be informed by a focus group of interviewers [52].

## Discussion

This programme of work focusses on formal support at home from health and social services to complement informal support provided by family and friends. It includes: supportive practical and emotional help; structured therapeutic interventions, such as counselling; and education, including training in managing behaviour [53]. This trial was designed to fill a knowledge gap identified by preceding systematic review [54]. It also took account of another recent study within the programme, which showed that people with dementia prefer advice on memory aids to be provided at home by a trained worker [55].

There is little evidence on the effectiveness and cost-effectiveness of support for people with dementia and their carers [56–58]. Nevertheless, English health and social care policy continues to emphasise the importance of early diagnosis and support for people with dementia living in their own homes [59, 60]. This assumes that this will improve the quality of life of people with dementia. If so this needs an evidence-based framework for a national pathway with an affordable implementation plan to improve the quality of post-diagnosis dementia care [60].

There are benefits to health and social care from knowing what forms of home support enhance patients’ experience and management of symptoms, over what is currently available. The trial will contribute to this evidence base if the intervention is clinically effective and cost-effective. It is hypothesised that by supporting the cognitive abilities of people with early dementia, memory aids, and training and support in their use, may improve their function, health and well-being and that of their carers. This trial will therefore evaluate the effects on people with dementia and their carers of this modest intervention, designed to be cheap, realistic and scalable [61].

It is planned to present findings to professionals who care for people with dementia; and to submit them for publication in journals reporting research into assistive technologies. These findings will also inform other studies within the programme, notably, economic modelling of the effects of different home support packages and the development of a toolkit for managers and commissioners, likely to be publicly available online with one module dedicated to findings from this trial.

### Trial status

This trial is currently recruiting. Recruitment started in November 2016 (first enrolment 6 December 2016) and is due to continue through 2018.

## Abbreviations

ACCEPT: Acceptance Checklist for Clinical Effectiveness Pilot Trials
BADLS: Bristol Activities of Daily Living Scale
CASP-19: Control, Autonomy, Self-realisation & Pleasure 19-item measure of quality of life
CDR: Clinical Dementia Rating scale
CEAC: Cost-effectiveness acceptability curves
CONSORT: Consolidated Standards of Reporting Trials
CRN: Clinical Research Network
CSRI: Client Service Receipt Inventory
DEMQOL: Dementia Quality of Life measure
DESCANT: Dementia Early Stage Cognitive Aids New Trial
DMEC: (Trial) Data Monitoring and Ethics Committee
DSP: Dementia Support Practitioner
GHQ: General Health Questionnaire
HoSt-D: Home Support in Dementia
ICECAP-O: Investigating Choice Experiments: Capability measure for Older people
LSNS-R: Lubben Social Network Scale – Revised
NHS: National Health Service
NIHR: National Institute for Health Research
PANT: Practitioner Assessment of Network Type
PI: Principal Investigator
PIS: Participant information sheet
PPCRG: Public, Patient and Carer Reference Group
PSC: Programme Steering Committee
PSSRU: Personal Social Services Research Unit
QALYs: Quality-Adjusted Life Years
R-IDDD: Revised Interview for Deterioration in Daily living activities in Dementia
RUD: Resource Utilisation in Dementia
S-MMSE: Standardised Mini-Mental State Examination
SSCQ: Short Sense of Competence Questionnaire
STU: Swansea Trials Unit
TAU: Treatment as usual
TDM: Trial Data Manager
TIDE: Together in Dementia Everyday
TM: Trial Manager
TSC: Trial Steering Committee
UCL: University College London
WTP: Willingness to pay
